## Abstract

**Background:**

Shoulder problems are a common complaint of the musculoskeletal system. Physical therapists treat these patients with different modalities such as exercise, massage, and shoulder taping. Although different techniques have been described, the effectiveness of taping has not yet been established. The aim of this study is to assess the effectiveness and cost-effectiveness of usual physical therapy care in combination with a particular tape technique for subacromial impingement syndrome of the shoulder compared to usual physical therapy care without this tape technique in a primary healthcare setting.

**Methods and design:**

An economic evaluation alongside a randomized controlled trial will be conducted. A sample of 140 patients between 18 and 65 years of age with a diagnosis of subacromial impingement syndrome (SAIS) as assessed by physical therapists will be recruited. Eligible patients will be randomized to either the intervention group (usual care in combination with the particular tape technique) or the control group (usual care without this tape technique). In both groups, usual care will consist of individualized physical therapy care. The primary outcomes will be shoulder-specific function (the Simple Shoulder Test) and pain severity (11-point numerical rating scale). The economic evaluation will be performed using a societal perspective. All relevant costs will be registered using cost diaries. Utilities (Quality Adjusted Life Years) will be measured using the EuroQol. The data will be collected at baseline, and 4, 12, and 26 weeks follow-up.

**Discussion:**

This pragmatic study will provide information about the effectiveness and cost-effectiveness of taping in patients presenting with clinical signs of SAIS.

**Trial registration:**

Trial registration number: NTR2575

## Background

Shoulder problems are a common complaint of the musculoskeletal system. It is the second most common musculoskeletal disorder following low back pain [1] and results in high morbidity [2]. Of all shoulder problems, subacromial impingement syndrome (SAIS) is the most frequent diagnosis [3], accounting for 44-65% of all shoulder problems [4-6]. In general, SAIS (also known as external impingement) is defined as the entrapment of the rotator cuff and subacromial bursa between the humerus and the coracoacromial arch [7].

Patients with SAIS are commonly treated by a physical therapist (PT). Various therapeutic options have been described, however, most are lacking a rigorous scientific background and there is uncertainty about the associated costs [8]. Some reviews have reported that exercise and manual treatment are most effective in relieving pain and improving function in SAIS, but the evidence for effectiveness is still under debate [8,9].

A promising modality in physical therapy is the application of taping. The essential function of the tape is to provide support during movement. However, research indicates that the tape also plays a role in decreasing the upper trapezius muscle activity [10] and offers a constant input on the proprioceptive system of the upper body muscles which support the active movement [11].

Three studies have examined the clinical effects of taping patients with SAIS using leukotape in combination with fixomull stretch (BSN medical^®^) [12-14]. In a pilot study of 22 patients with unilateral shoulder pain of more than six weeks, Miller et al. [12] compared taping as an adjunct to usual physical therapy with usual physical therapy alone. They found a strong trend toward reduced pain and improved function in favor of scapular taping at two weeks. The magnitude of these differences was reduced at a follow-up at six weeks. Case studies of taping patients with SAIS have been published by Host et al. [13] and Shamus and Shamus [14]. Both studies found a reduction in pain and an improvement of function. In sum, the effects in pain relief and improving shoulder function due to shoulder taping looks promising. However, study samples were small or had no control group. In addition, tape techniques vary and we must conclude that the evidence for its usefulness is still limited. Therefore, the primary aim of this study is to assess the effectiveness and cost-effectiveness of usual physical therapy care in combination with one particular tape technique for subacromial impingement syndrome of the shoulder compared to usual physical therapy care alone in a primary health care setting.

## Methods/Design

### Design

An economic evaluation will be conducted alongside a randomized controlled trial (RCT). Figure 1 provides an overview of the study design. Outcomes will be measured at baseline, 4, 12 and 26 weeks follow-up.

**Figure 1 F1:**
[figure not shown]
**Design of the study**.

### Setting

A sample of 140 patients between 18 and 65 years of age with clinical signs of SAIS will be recruited from the primary physical therapy setting in the Netherlands between September 2010 and November 2011.

### Ethical approval

The Medical Ethics Committee of the VU University Medical Centre in Amsterdam has approved the study protocol (registration number: 2010\119).

### Study population

To be eligible for the trial, patients must meet the following criteria as assessed by the participating PTs; Two positive impingement tests indicating SAIS (see section impingement tests), age between 18 and 65 years, and accepting the consequences of participation in the study. Patients will be excluded if they have a primary SAIS (anatomical abnormalities as scapulohumeral joint dysplasia, total cuff tear etc. confirmed with radiography and/or diagnostic ultrasound with exception of calcifications, minor arthrosis, and partial cuff tears]), been operated previously at the shoulder or cervical spine, a rheumatic disease such as polymyalgia rheumatica, rheumatoid arthritis, lupus erythematosis and fibromyalgia, a severe arthritis of the glenohumeral joint, had three or more subacromial corticosteroid injections in the last year, a (suspected) severe disease such as malignancy, had severe trauma of the shoulder in the last 6 months, a neurologic disease with negative consequences for the shoulder (such as cerebral vascular accident, multiple sclerosis, Parkinson's disease), type II diabetes, had a luxation or fracture of the affected shoulder, a cervico-radicular syndrome, a pathology of organs with negative consequences for the shoulder, dementia, a psychiatric disease, an insufficient understanding of the Dutch language, a bad condition of the skin around the shoulder because of a skin disease, and an allergy to tape.

### Recruitment of patients

At the first consult, PTs will inform all eligible patients who attend their primary care clinic about the study and will assess patients for the in- and exclusion criteria. Patients will be further instructed about the study through a patient information letter. For patients interested in participating, the PT will provide contact details of the patients to the investigators. One of the investigators will phone the patient before the second consult to answer potential questions and to provide information. If the patient decides to participate, they will be asked to fill in baseline questionnaires (digital or paper) before the second physical therapy consult. At the second consult, the patient will sign an informed consent form. Thereafter, the PT will open a numbered opaque sealed envelope containing the treatment allocation (i.e. usual physical therapy care in combination with one particular tape technique or usual physical therapy care without this tape technique).

### Treatment allocation

Prior to the study, every practice will receive 10 to 20 concealed envelopes, which contain an allocation to one of the two treatment strategies. The randomization process will be generated by computer. To prevent unequal treatment-group sizes, the patients will be randomized according to a stratified block randomization method, in blocks of four. The PTs will not know the sequence of the treatment allocation codes of each practice to guarantee allocation concealment.

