### Blinding

The treating PTs and patients cannot be blinded for the treatment allocation because of the knowledge of receiving the modality. The investigators, who will conduct the data collection and data entry, will not be blinded. However, almost all outcome measures will be collected using questionnaires without personal contact with the patient. The participating statistician will perform the analyses blinded for treatment allocation.

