### Sample size

Power calculations, based on the studies carried out by Santamato et al. [35] and Tashjian et al. [36] were performed for the 2 main outcomes (power 0.95; alpha 0.05). To detect a clinically relevant mean difference between the two treatment groups of 2 points on the SST [36] (standard deviation [SD] 2), 26 patients are needed per group. To detect a clinically relevant mean difference of 2 points (SD 3) for pain (11-point NRS) [35], 2 groups of 59 patients are needed. Anticipating a potential drop-out of 15%, 70 participants per treatment group (total n = 140) will be recruited.

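### Fixed blocks of four per practice, opened by the unblinded therapist who recruits, let later allocations be deduced, so the claimed guarantee of concealment does not hold

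*Protocol article*

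**What the plan says.** Under Treatment allocation, "every practice will receive 10 to 20 concealed envelopes" before the study starts. The list is computer-generated and "the patients will be randomized according to a stratified block randomization method, in blocks of four". The same section then states: "The PTs will not know the sequence of the treatment allocation codes of each practice to guarantee allocation concealment". The stratification factor is not named. That it is the practice is inferred from the envelope sets and codes being held per practice.

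Under Recruitment of patients, therapists inform eligible patients at the first consult and "will assess patients for the in- and exclusion criteria". An investigator then phones the patient, and the baseline questionnaires are completed before the second consult. At the second consult the patient signs consent. "Thereafter, the PT will open a numbered opaque sealed envelope containing the treatment allocation".

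Under Blinding: "The treating PTs and patients cannot be blinded for the treatment allocation". Under Sample size, "70 participants per treatment group (total n = 140) will be recruited", which implies 1:1 allocation and hence two of each arm in a block of four.

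Under Physical therapists, the therapists receive a detailed manual of the study protocol. The article does not say that block size is given to them, nor that it is withheld.

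**The concern.** Concealment requires that the next allocation cannot be foreseen when a patient is being considered for the trial. Not seeing the list is one part of that. The other part is not being able to reconstruct it. In an open-label trial with a fixed block size, a practice that keeps track of its own numbered envelopes knows the last allocation of each block, and the last two whenever the first two match.

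Here one role combines eligibility assessment, opening the envelope and unblinded treatment. A foreseeable allocation could influence how a borderline impingement test is judged, or whether and when a patient is entered. Both primary outcomes are self-reported by patients who know their treatment, so sound allocation is a main protection of the comparison. Selection on prognosis that nobody has measured cannot be repaired in the analysis.

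**Working it through.** **Inputs.** Block size 4 and 10 to 20 envelopes per practice (Treatment allocation); 1:1 allocation, pain target difference 2 and SD 3 (Sample size). The article gives no figure for predictability, so there is none to reproduce. Its sample sizes do reproduce (26, 59, and 59/0.85 = 69.4, rounded up to 70) and play no part in the finding beyond supplying the SD and the target.

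**1. Certain allocations in a 2+2 block.** There are 6 equally likely orders. An allocation is certain once one arm is used up.
- Positions 1 and 2: never.
- Position 3: when the first two match, probability 2/6 = 1/3.
- Position 4: always.
- Share: (0 + 0 + 1/3 + 1)/4 = 1/3.

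The best guess is right (1/2 + 2/3 + 2/3 + 1)/4 = 17/24 = 70.8% of the time, against 50% without blocking.

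**2. Actual envelope sets.** Each complete block yields 4/3 certain allocations.
- 10 envelopes: 2 × 4/3 = 2.67, or 26.7%.
- 12, 16 or 20 envelopes: 33.3%.
- Other sizes from 10 to 20 lie between these.

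**3. Several therapists per practice (k), sharing patients equally, each seeing only their own allocations.** Certainty requires that the therapist handled both patients who used up one arm, which has probability 1/k². The share becomes (1/3)/k²:
- k = 2: 1/12 = 8.3%
- k = 3: 1/27 = 3.7%
- k = 4: 1/48 = 2.1%

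**4. The gap between consults.** Suppose the therapist sees everything, but one other patient of the practice is allocated between the eligibility decision and the envelope. Only position 4 can then be certain, and only when the first two matched: (1/3)/4 = 1/12 = 8.3%. With two patients in between it is 0%.

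**5. Illustrative consequence for pain.** Assume that at each certain allocation the therapist enters a patient whose outcome is shifted by s points, in opposite directions for the two arms. Bias = 2 × share × s. With about 60 analysed per arm and SD 3, SE = 3 × √(2/60) = 0.548. Rejection under no effect = 1 − Φ(1.96 − bias/SE) + Φ(−1.96 − bias/SE).

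| Certain share | Shift s | Bias (points) | Type I error |
|---|---|---|---|
| 1/3 | 1.0 | 0.67 | about 23% |
| 1/3 | 0.5 | 0.33 | about 9% |
| 8% | 1.0 | 0.16 | about 6% |
| 4% | 1.0 | 0.08 | about 5% |

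The shift is an assumption; nothing in the article gives it. A 1-point shift each way is a 2-point gap between steered patients, as large as the trial's whole target difference. No baseline adjustment is included.

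**6. Effect of varying the block size.** Simulation with 20 patients per practice and a therapist who knows the set of sizes but not their order: mixed blocks of 4 and 6 leave about 6% certain, and 2, 4 and 6 about 4%. Best-guess success falls only to about 69% for 4 and 6, and about 70% for 2, 4 and 6.

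**The case against.** A reader might infer that one third of allocations will in fact be known in advance and that the type I error will be near 23%. The article does not support that. It does not say therapists are told the block size, and publishing it in an article does not show that they use it. The analysis model has separate levels for therapist and practice, so practices with several therapists are expected, which lowers the share sharply. Eligibility is judged one consult before the envelope is opened, so the prediction has to be made ahead and fails when other patients are allocated in between. The plan says therapists inform all eligible patients and gives them a standardised checklist, so selective invitation would depart from the protocol. Numbered, opaque, sealed envelopes opened after consent are recognised safeguards. All of this stands, and it makes the one-third figure a ceiling.

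A reader might also infer that any resulting bias is wholly beyond repair. That too goes further than the article allows. Baseline pain and function are recorded before allocation, baseline is in the mixed model, and uneven prognostic factors are to be corrected for. Steering on measured severity would be at least partly handled; unmeasured prognosis would not.

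The remedy hardly moves best-guess success if the sizes become known. That is correct, and is why withholding them matters.

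What these points do not answer is the stated reasoning. Sealed envelopes and an unseen list do not prevent deduction from past allocations, and nothing in the article says that sizes vary, are withheld, or that allocation is central.

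**Conclusion.** The point holds as a conditional risk together with an overstated claim. The design as described does not guarantee concealment. The certain share is at most 26.7% to 33.3% for the planned envelope sets, given a therapist who knows or infers the block size and sees all earlier allocations in the practice. It is about 8%, 4% or 2% with 2, 3 or 4 therapists who see only their own patients, and lower again when patients overlap between consults. The article does not give the number of therapists per practice, so the share cannot be narrowed further.

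The bias of 0.67 points, a third of the 2-point target, is a worst case in which every therapist steers at every certain allocation. At an 8% share the same steering has little effect. The result assumes that practice is the stratum, which the text strongly implies but does not state. This is a worthwhile, cheap improvement to the design; the article contains no wrong figure on this point.

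**What to change.** Generate each practice's list with randomly varying block sizes, for example 4 and 6. Keep the sizes out of the study manual and away from the therapists, and replace unopened envelopes from the new lists. Name the stratification factor. In place of the guarantee, state what the design supports: numbered, opaque, sealed envelopes opened after consent, with block sizes that vary and are not disclosed to those who recruit.

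The cost is a re-run of the computer list and a reprint of unopened envelopes. The largest possible imbalance between arms within a practice rises from 2 to 3.

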### Impingement tests

Many different diagnostic criteria for the SAIS have been suggested [15]. In general, clinicians base the diagnosis of SAIS on the history of the patient and specific signs and symptoms. Research findings suggest that single tests have limited use in informing diagnosis and a combination of tests improves clinical utility [9,15]. For the present study, two or more positive well-known SAIS tests will indicate a SAIS, which is in concordance with previous pragmatic studies [16]. The following SAIS tests will be used: the painful arc of abduction test [17], the empty can test (Jobe test) [18], the external rotation resistance test [19] and the Hawkins-Kennedy test [20]. The reliability of all tests is acceptable for clinical use [15].

### Physical therapists

All patients will be treated by PTs of the participating clinics. Prior to the study, all PTs will follow a 1½-hour training session in which the rationale of the study will be described and discussed, and the taping method will be instructed and trained. The PTs will receive a detailed manual of the study protocol including a standardized eligibility checklist, and a description of the impingement tests and the taping technique.

### Tape method

Patients who are allocated to usual physical therapy in combination with tape will be treated at the end of each treatment session for at least 4 weeks by a modified tape technique after Shamus and Shamus [14]. In this technique, the arm of the patient lays on the treatment table, with the shoulder in 80° abduction in the plane of the scapula (Figure 2). Two strips of rigid tape (leukotape, BSN medical^®^) will be placed upon two strips of elastic tape (fixomull stretch, BSN medical^®^) without tension. When the arm of the patient is brought back to a relaxed position along the body, the arm will be slightly abducted from the body (approximately 10°) due to the tension of the tape (Figure 3). The tape will be worn for a minimum of 2 and a maximum of 7 days. Tape will be worn for short periods (2-3 days) for patients with severe pain and at the beginning of the tape period, and longer for patients with less pain and who are familiar with wearing the tape. In addition, patients with severe pain will be taped with the shoulder in less abduction (50-70°) so that the tape produces less tension when the arm is in the relaxed position. At least one to two days before the next treatment, the tape will be removed by the patient in order to let the skin recover from the tape. The PT is free to determine the abduction angle of the shoulder in which the shoulder will be taped, the exact days the tape will be worn and the number of treatments per week in order to reflect clinical practice. During the first 4 weeks, the treatment with tape will be stopped if the patient is free of pain, allergic to tape or reports a substantial increase in complaints because of the tape.

**Figure 2 F2:**
[figure not shown]
**The tape is applied to the shoulder in 80° abduction and 30° forward flexion**.

**Figure 3 F3:**
[figure not shown]
**In a relaxed position, the arm hangs in slight abduction due to the tension of the tape**.

### Usual care

Usual care will consist of individualized tailored physical therapy. The content of treatment, i.e. the choice of interventions, is at the discretion of the PT. In general, therapy is expected to include exercises to improve mobility and muscle function, passive mobilizations, instructions (posture and movement), massages and ice packages [8]. Furthermore, if the patient is not allocated to usual care in combination with shoulder taping, the use of kinesiotape will be allowed. In the Netherlands, kinesiotape is frequently used, but the theoretical concept, the tape structure, and the techniques are not comparable to the tape and tape technique used in this study [21,22]. During the first four weeks the patients are requested not to receive any co-interventions (such as complementary and/or alternative medicine [CAM], injection therapy or surgery). The use of (pain) medication is allowed in both groups.

For both interventions the number of treatment sessions, the treatment modalities, the treatment goals, any deviations from the protocol, and reasons for prematurely terminating treatment (e.g. skin problems due to the tape) will be recorded. In addition, PTs in both groups familiar with the classification system described in Cools and Walravens [23] will classify the patients according to this system, in order to identify subgroups that respond best to the tape technique used. The principal investigators will regularly monitor the PTs for compliance with the treatment protocols, by means of phone calls and e-mail contact.

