## Discussion

Few studies have been performed evaluating the clinical effects of taping shoulders in patients presenting clinical signs and symptoms of SAIS, although some promising results have been reported [12-14]. It is interesting to note that there have been some studies for other patient populations using leukotape in combination with fixomull stretch. Peterson [42] described a taping technique with electrical stimulation in one patient with central cord syndrome and bilateral shoulder subluxation and concluded that the shoulder taping along with electrical stimulation and a rehabilitation program may have played a role in the reduction of the patient's shoulder subluxation. In a RCT, the effect of shoulder taping in 98 patients with a stroke was studied [43]. They found a non significant trend for less pain and better function in strapped patients after 6 weeks. Finally, a number of authors have investigated the effect of shoulder taping on electro-activity of shoulder muscles, but their findings are contradictory [10,11,44,45].

In sum, the use of shoulder taping is a promising modality in improving outcomes on pain relief and function improvement in those presenting to primary physical therapy care with signs and symptoms of SAIS, however the method has not been adequately tested.

To our knowledge this is the first RCT examining the possible additional effect of taping using a modified technique according to Shamus and Shamus [14] compared to usual physical therapy alone in primary care patients presenting with signs and symptoms of SAIS. In addition, it includes the first economic evaluation on taping for SAIS.

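### Kinesiotape is permitted only in the control arm, which does not fit the stated question of tape added to usual care alone

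*Protocol article*

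**What the plan says.** The Usual care section of the protocol article leaves the content of therapy to the therapist and then adds one rule that depends on allocation: "if the patient is not allocated to usual care in combination with shoulder taping, the use of kinesiotape will be allowed". It goes on: "In the Netherlands, kinesiotape is frequently used, but the theoretical concept, the tape structure, and the techniques are not comparable" to those of the study tape.

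The article describes the comparator in two ways.

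- **Care without the study technique.** The Abstract (Methods and design) has "the control group (usual care without this tape technique". The aim in the Abstract's Background paragraph and the allocation text under Recruitment of patients use the same description.
- **Usual care alone.** The aim at the end of the Background section is the study tape plus usual care "compared to usual physical therapy care alone in a primary health care setting". The last paragraph of the Discussion calls the trial "the first RCT examining the possible additional effect of taping", again relative to usual physical therapy alone.

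The Abstract also states: "In both groups, usual care will consist of individualized physical therapy care".

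Treatment modalities are to be recorded in both groups (Usual care). The per-protocol definition under Data-analysis covers untreated patients, early withdrawal, and treatment not according to allocation.

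**The concern.** An add-on question requires the same background care in both arms, so that the study tape is the only planned difference. Here a common modality is available to controls and, by implication, not to patients in the tape arm. If a therapist would normally use kinesiotape for a given patient, that patient may receive it as a control, but in the tape arm the study tape takes its place.

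That the two tapes differ in concept and technique shows that they are different interventions. It does not show that kinesiotape has no effect. Patients and therapists are unblinded (Blinding) and both primary outcomes are self-reported, so an expectation effect of being taped could also act in controls.

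What is at stake is the meaning of the primary result and of the cost-effectiveness ratios built on it. Under the add-on wording, a null result would be reported as the tape adding nothing to usual care. Part of the control arm may have been taped in another way, so the data would not support that sentence.

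**Working it through.** **1. Is the rule really asymmetric?** The article does not word the tape-arm exclusion as a ban. The inference rests on the conditional wording. It is strengthened by the same paragraph, which explicitly allows pain medication in both groups and asks patients to avoid co-interventions without distinguishing arms. Kinesiotape is the only background item tied to allocation.

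**2. What does each comparator wording estimate?** Let t be the mean effect of the study tape over usual care without kinesiotape, p the share of controls given kinesiotape, and e its mean net effect in those patients, on the same scale. Relative to usual care without kinesiotape:

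- tape arm: t
- control arm: p × e
- difference between arms: t − p × e

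Under the wording 'without this technique', t − p × e is the intended quantity. Under 'alone' and 'additional effect', read as otherwise identical care, the intended quantity is t. The two agree only if p × e = 0.

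**3. How far apart could they be?** The documents give neither p nor e. For illustration only, assume t = 2 points on the pain scale.

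| p | e (points) | t − p × e |
|---|---|---|
| any | 0 | 2.0 |
| 0.2 | 0.5 | 2 − 0.1 = 1.9 |
| 0.4 | 1.0 | 2 − 0.4 = 1.6 |
| 0.6 | 1.5 | 2 − 0.9 = 1.1 |
| 0.4 | −1.0 | 2 + 0.4 = 2.4 |

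The last row shows that the direction also depends on an assumption.

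**4. Is the sample size affected?** The plan's own figures, two-sided alpha 0.05 and power 0.95, with n per group = 2 × (1.960 + 1.645)² × SD² / difference²:

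- Simple Shoulder Test: 2 × 12.996 × 4 / 4 = 25.99, so 26 (stated 26)
- Pain: 2 × 12.996 × 9 / 4 = 58.5, so 59 (stated 59)
- Drop-out: 59 / 0.85 = 69.4, so 70 per group and 140 in total (as stated)

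The Sample size section sets the 2 points as a relevant difference between the two treatment groups, that is, between the arms as designed. Power for that difference stays at 95% whatever p and e are.

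**5. Does the current plan already resolve it?** Recorded modalities show which controls received kinesiotape. They cannot show who in the tape arm would have received it, so no like-for-like subgroup can be formed afterwards. Permitted kinesiotape in a control is not a deviation, so the per-protocol analysis does not address it.

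**The case against.** The strongest reply is that this is an openly stated, pragmatic choice. The Abstract and the recruitment text define the control as care without the particular technique, which kinesiotape does not breach. The Background aim also concerns one particular technique, not tape in general. If kinesiotape is part of Dutch usual care, it belongs in the comparator, and so does its cost. Its use is recorded, so a null result can be read against the observed rate.

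Most of this stands. The strategy comparison is coherent, and including kinesiotape costs among controls is no defect under it. What remains is that the article states a second question, in the Background aim and the Discussion, which this design does not answer. Disclosing the rule in Usual care does not correct those statements.

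A reader might go further and infer that the article contradicts itself throughout, or that power is lost. The first fails because the control definition in the Abstract and recruitment text fits the rule. The second fails because it needs assumed values of p and e, and it moves the 2 points from the arms as designed to a comparator without kinesiotape.

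**Conclusion.** The point holds as a mismatch between the kinesiotape rule and two statements of the trial's question: the aim in the Background section and the closing claim in the Discussion. It limits what may be concluded. The trial can compare study tape plus usual care with usual care that may include kinesiotape. It cannot, as planned, isolate what the tape adds to otherwise identical care, and a null result should not be reported in those terms.

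The size and direction of the gap between the two questions cannot be derived from the documents. It is zero if kinesiotape is unused or has no net effect. The range in the working rests wholly on assumed values. The sample size reproduces, and its power statement stands. The conclusion assumes that the conditional wording means kinesiotape is not used in the tape arm, which the article implies but does not say.

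**What to change.** 1. Reconcile the Background aim and the last paragraph of the Discussion with the Usual care section, so that one comparator is stated throughout, and say explicitly what applies to kinesiotape in the tape arm. Which rule applies is for the sponsor to decide. If the present rule stays, word the objective and conclusion as study tape technique plus usual care versus usual care that may include kinesiotape, and drop 'alone' and 'additional effect'. Label the cost-effectiveness results in the same way.
2. Add one yes/no item to the existing eligibility checklist, completed before the envelope is opened: would kinesiotape be part of this patient's usual care? Eligibility is assessed at the first consult and the envelope is opened at the second, so the timing allows it.
3. Pre-specify a supportive estimate of the treatment effect among patients marked 'no'. Because the item precedes allocation, this is a valid randomised comparison, and in these patients usual care is intended to be the same in both arms.
4. Report kinesiotape use in controls from the modalities already recorded, and use it to check whether the stated intent held.

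**Cost.** One tick box, one supportive analysis and changes of wording. The claim becomes narrower. The stratum estimate depends on the therapist's stated intent and is less precise. With 59 evaluable patients per group and SD 3, the 95% half-width for a simple comparison of mean pain is 1.96 × 3 × √(2/59) = 1.08 points. If 80% of patients are marked 'no' it is 1.08 / √0.8 = 1.21, and if 40% are, 1.08 / √0.4 = 1.71. These shares are assumptions. The estimate should therefore be presented as supportive only.
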